#### Measurement protocol

All items to be assessed are in Table 1 and include both individual and area-level measures. At recruitment, accelerometers (Actigraph GT3X) and GPS devices (Canmore) on an elastic belt and saliva collection kits will be distributed, and data will be collected for the following week. For subsequent time points, participants will be phoned to arrange an equipment delivery time and schedule a health appointment. Participants will be reminded via StANDApp (detailed below) and/or text to wear the elastic belt and to collect saliva samples. Participants will also take a paper survey at home. Participants will return the equipment, survey and saliva kits at the health appointment or, if they forget an item, will schedule a time to return the item(s) in order to receive the compensation voucher.

**Table 1 Tab1:** Tools, scale of measurement, and measurements that will be obtained annually 2019–2024. Individual-level refers to measurements collected from individual household participants and area-level refers to measurements collected within and at some points around a park

Tool/Variable	Individual or area-level	Measures obtained
Survey	Individual	Demographics, perceptions of neighborhoods, disease and medication history, diet, perceived stress score, anxiety and depression symptoms, nature-relatedness, perceived safety, acute illness
Physical activity (PA)	Individual	Total activity counts, Moderate-to-vigorous PA, when combined with GPS – green PA
GPS	Individual	Time spent in park, time spent in view of park, when combined with PA – green PA
Cortisol samples	Individual	Total concentration, slope of cortisol from waking to evening
Dried blood spots	Individual	C-reactive protein
Finger-stick A1C	Individual	Hemoglobin A1C levels
Plant surveys	Area	Plant diversity of park, invasive species versus native species
SOPARC	Area	Usage of park
Signs of care	Area	Maintenance level of park
Bird surveys	Area	Bird diversity of park
360 imagery	Area	Greenness of park, negative visual exposures, signs of disorder
AudioMoth acoustic recorders	Area	Bird species, insects, sound diversity, noise
Weather station	Area	Daily precipitation, high temperature

At the health appointment, field staff will collect anthropometrics and dried blood spot (DBS) samples, measure A1C using test strips, and retrieve equipment and cortisol samples. All health data will be entered and then shared with each participant via a health results sheet, which includes resources for free or low-cost healthcare in Detroit.

### StANDApp smartphone app

In partnership with MEI Research Ltd., we have developed a secure mobile app for all study communication, scheduling, and retaining survey deployment. MEI’s PiLR [54] system will allow for the deployment of surveys as a form of monthly contact from the study team to increase retention, sharing health results with each participant, and reminders about health appointments, charging units and wearing belts and taking cortisol samples. Based on pilot work, we determined that some participants may be reticent to use this application on their mobile phone. Accordingly, we will use the app on a voluntary basis. All reminders will also be sent by text message, negating the requirement that all participants use the app.

### Physical activity (primary outcome) measured using accelerometry

PA and sedentary behavior are measured using the ActiGraph accelerometer (ActiGraph model GT3X; Pensacola, FL). The ActiGraph is a triaxial accelerometer that measures acceleration in three planes of motion. Accelerometers capture and filter acceleration signals that are digitized and recorded as count values that are stored in investigator-defined intervals. Raw data are stored and may also be used for analyses.

The accelerometers will be worn on an elastic waistband, placed at the right hip, for all waking hours over seven days at each of the study’s four measurement time points (all during the summer or early autumn). Data will be collected in raw mode (30 Hz) and aggregated to 1-min values for analyses. The primary outcome is total PA counts per week, which has been associated with cardio-metabolic outcomes and biomarkers [22]. Analyses will also include number of minutes spent at given PA intensity levels using cut-points of Freedson et al. (≥1952 cpm) for moderate-to-vigorous intensity PA and Matthews et al. (< 100 cpm) for sedentary behavior, with light PA as 100–1951 cpm [55, 56]. We will also explore PA intensity levels using vector magnitude cutpoints [57]. In addition, these measures will be stratified by whether the PA occurred in the study park, in any greenspace, or elsewhere (based on GPS data). This will provide an indication of the proportion of ‘green PA’ from total PA. Periods of 60 min or more of continuous zeroes are considered non-wear times and not included in the calculation of total wear time. To be included, we will require ≥4 days of PA data (wear time ≥ 8–10 h/day) per time point [58]. If high levels of missing data exist, imputation strategies will be utilized. PA data will be collected at the same time of year (summer months only) to account for seasonality.

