**Methods:**

The Study of Active Neighborhoods in Detroit is a quasi-experimental, longitudinal panel natural experiment with two conditions (restored park intervention (INT) and control (CNT)) and annual measurements at baseline and 3-years post-restoration. Individuals (sampled within 500 m of an INT/CNT park) serve as the unit of analysis. Restoration (*n* = 4 parks) involves replacing non-native plants and turf with native plants; creating trails; posting signage; and leading community stewardship events. The CNT condition (*n* = 5) is an unmaintained park, matched to INT based on specified neighborhood conditions. Recruitment involves several avenues, with a retention goal of 450 participants. Park measures include plant/avian diversity; usage of the park (SOPARC); signs of care; auditory environment recordings; and visual greenness using 360 imagery. Health outcomes include device-based physical activity behavior (primary outcome); salivary cortisol (secondary outcome); and several downstream health outcomes. Exposure to the INT will be assessed through visual contact time and time spent in the park using GPS data. Changes in health outcomes between years and INT versus CNT will be tested using generalized linear (mixed) models.

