To address missingness in our response data, we will employ strategies for imputation [139]. The techniques described above allow missing at random (MAR). Inverse probability weighting [140] will be investigated to accommodate missing data patterns that are not MAR. To minimize bias in analysis, we will adjust for factors that may be unbalanced between groups and examine the robustness of our conclusions under deviations of model assumptions. Below, we outline specific analyses for each hypothesis to be tested.

#### Hypothesis 1

We will separately evaluate average activity counts/minute and average moderate-to-vigorous minutes over the one-week observation period for each of the data collection periods. The predictor of interest is binary: INT versus CNT.

#### Hypothesis 2

The primary outcome, ‘green PA’, will be average activity counts/minute and average moderate-to-vigorous minutes over the one-week observation period while in parks and greenspaces in Detroit, as a subset of all activity.

#### Hypothesis 3

We hypothesize there will be an association between PA and the visual and auditory exposures. Instead of a binary predictor of interest, we will use continuous predictors for visual and auditory park exposures. Interaction terms between positive and negative exposures will also be assessed, as evidence suggests that negative sounds deplete the restorative benefits of natural sounds, [141] and that parks are often dominated by noise [45, 142].

#### Hypothesis 4

Each stress outcome will be evaluated separately and treated continuously. We will also explore potential mediators (e.g., PA) by adding each to mixed models as fixed terms, and adjusted mediation and partial correlation coefficients explored. We will adjust for prescription medication history and symptoms of acute illness as potential confounders.

#### Hypothesis 5

We will assess relationships with each stress indicator, in turn.

#### Hypothesis 6

We hypothesize there will be an association between each stress indicator and these exposures.

#### Hypothesis 7

We will compare INT and CNT groups from baseline through three-years post-restoration for changes in CRP and A1C (continuously measured) between INT and CNT groups. We will also consider the inclusion of prescription medication history and symptoms of acute illness as potential confounders.

#### Hypothesis 8

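### The declared primary outcome (the weekly activity-count total, with no stated wear-time scaling) is not the variable on which Hypothesis 1 is analysed

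*Protocol article*

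**What the plan says.** The abstract fixes only the domain: "Health outcomes include device-based physical activity behavior (primary outcome". The accelerometry section gives the metric: "The primary outcome is total PA counts per week". It adds minutes at each intensity level as further analyses.

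Under Statistical analysis, Hypothesis 1 reads "We will separately evaluate average activity counts/minute and average moderate-to-vigorous minutes over the one-week observation period". Hypothesis 2 then reads "The primary outcome, ‘green PA’, will be average activity counts/minute and average moderate-to-vigorous minutes over the one-week observation period", restricted to activity in parks and greenspaces. The weekly total is not named under any of the eight hypotheses.

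On wear, the belt is to be worn "for all waking hours over seven days at each of the study’s four measurement time points". The entry rule is "To be included, we will require ≥4 days of PA data", with a daily minimum written as a range from 8 to 10 hours. An hour or more of continuous zeroes is treated as non-wear and left out of total wear time. Imputation is foreseen if much data is missing, without a trigger. The section does not say that the weekly total is scaled by hours or days worn.

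The Sample size section defines the effect as a difference-in-differences in physical activity from baseline to three years. It uses a standardised effect of 0.35 and names no metric.

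**The concern.** A confirmatory test needs one variable. Here the section that declares the primary outcome and the section that says how Hypothesis 1 will be examined name different ones, and the second names two without ranking them. If they disagree at the end of the study, this document does not say which result is the headline.

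The choice matters because the candidates respond differently to wear. A sum over whatever was recorded rises with hours worn. A rate per minute of valid wear largely does not. If wear in one group drifts relative to the other over the study, the unscaled total can show an effect that is not there or hide one that is. Wear variation unrelated to group adds noise. The floating daily minimum also leaves open which days, and so which participants, are analysed.

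**Working it through.** **1. The plan's own figure.** Inputs from Sample size: effect 0.35, r = 0.35, ICC = 0.004, 50 per park, 4 intervention and 5 control parks (200 and 250 people), two-sided 5%. Note 1/200 + 1/250 = 0.009.

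- Change-score variance times design effect: 2(1 − 0.35) × (1 + 49 × 0.004) = 1.3 × 1.196 = 1.555. SE = √(1.555 × 0.009) = 0.1183. Power = Φ(0.35/0.1183 − 1.96) = 84.1%.
- Park effects independent across occasions: 2(1 − 0.35 − 0.004) + 2 × 50 × 0.004 = 1.692. SE = 0.1234, power 81.0%.
- Attrition: 620 × 0.85 × 0.90 × 0.95 = 450.6.

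The stated 82%, 450 and 620 are reproduced closely enough. None of these inputs depends on the activity metric.

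**2. The definitions side by side.**

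- Abstract: domain only.
- Accelerometry section: weekly total, declared primary.
- Hypothesis 1: counts per minute and moderate-to-vigorous minutes, separately.
- Hypothesis 2: the greenspace versions of those two, called primary.
- Sample size: activity, no metric.

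The denominator of counts per minute is not stated. If it were all 7 × 24 × 60 = 10,080 minutes of the week, the measure would be the weekly total divided by a constant. If it is valid wear minutes, it is a different variable.

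**3. Range of wear that the entry rule admits.**

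- 4 days × 8 h = 32 h; 7 days × 10 h = 70 h. Ratio 70/32 = 2.2 at equal counts per minute.
- Assuming full waking wear of 14 to 16 h on 7 days: 98 to 112 h. Ratio to 32 h: 3.1 to 3.5.

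These compare individuals at the ends of the range, not groups.

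**4. Bias in the difference-in-differences.** With activity unchanged, mean weekly total is proportional to mean wear. Let δ be the relative change in wear from baseline to year 3. In SD units the bias is (δ_INT − δ_CNT)/CV, where CV is the coefficient of variation of the weekly total. The document gives no CV; 0.3 to 0.5 is assumed.

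- 5% differential change: 0.05/0.5 = 0.10 to 0.05/0.3 = 0.17 SD, which is 29% to 48% of 0.35.
- One day in seven (14.3%): 0.29 to 0.48 SD.
- Differential change equal to the whole design effect: 0.35 × 0.3 = 10.5% to 0.35 × 0.5 = 17.5%.

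**5. Noise.** On the log scale, Var(total) = Var(counts per minute) + Var(wear) if the two are independent. With an assumed between-person CV of counts per minute of 0.3 to 0.5, the share due to wear is:

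- 24% to 45% if valid days are uniform on 4–7 and hours uniform on 8–14;
- 17% to 35% if half wear all 7 days and hours average 13;
- 8% to 17% if all wear 7 days with hours uniform on 10–16.

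As an illustration, suppose 0.35 applies to counts per minute and wear contributes a share s of the variance of the total, independently between occasions. The effect becomes 0.35√(1 − s) and r becomes 0.35(1 − s). In the first power formula:

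- s = 0.15: effect 0.32, power 75% (78% if r stays at 0.35).
- s = 0.30: effect 0.29, power 63% (70% if r stays at 0.35).

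The comparison is with 84%.

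**The case against.** The strongest reply is that the hierarchy is clear (activity primary, stress secondary), that how a total is scaled for wear is analysis-plan detail, and that the per-minute measure shows wear was considered. Silence on scaling would indeed be no finding alone. But naming one outcome as primary and analysing the hypothesis on others is a contradiction within this document, and the daily minimum is given here as a range. The per-minute measure resolves the wear problem only if its denominator is valid wear, which is not said.

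It is also fair that only a differential change in wear biases the contrast, and the document gives no evidence that one will occur. The accelerometry section gives a reason for total counts too, namely their association with cardio-metabolic outcomes and biomarkers.

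Several stronger readings are tempting and not supported:

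- **That the weekly total measures compliance as much as activity.** No variances are given, and the wear share was 8% to 45% in the scenarios tried.
- **That there are three rival primary outcomes.** The word primary under Hypothesis 2 can mean primary for that hypothesis only. The firm conflict is between the accelerometry section and Hypothesis 1.
- **That the wrong coefficient is tested**, because the Hypothesis 1 predictor is described as binary. That describes the exposure, as the contrast with continuous predictors under Hypothesis 3 shows. The model has group-by-time terms, and the baseline-to-year-3 contrast is stated.
- **That five activity variables give a family-wise error of 23%.** This pools two hypotheses, counts alternative definitions of one outcome as separate tests, and assumes independence. The two Hypothesis 1 variables give at most 1 − 0.95² = 9.75% if independent, and less if positively correlated.
- **That the headline will be picked after the data are seen.** The article cites a preregistration that is not shown and may name the metric.

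**Conclusion.** The point holds in this form: the declared primary outcome and the variables analysed for Hypothesis 1 differ, so the powered test has no single outcome in this document. Calling green activity primary under Hypothesis 2 adds ambiguity but is not a firm third definition.

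The wear problem is secondary but real for the metric as declared. The 2.2-fold range follows from the entry rule alone. The bias of 0.10 to 0.17 SD for a 5% differential change rests on the assumed CV of 0.3 to 0.5 and on a change that may not happen. The loss of power through noise rests on assumed wear distributions and on 0.35 applying to the per-minute rate. The stated sample size is not called into question by this point, because 0.35 is standardised and tied to no metric.

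**What to change.** - Name one primary outcome, in the same words, in the accelerometry section and under Hypothesis 1. It should be standardised for valid wear: for example, mean counts per valid wear minute with the denominator written out, or the weekly total scaled to valid wear time.
- State that the 0.35 effect size and the baseline-to-year-3 difference-in-differences refer to that outcome.
- Replace the 8-to-10-hour range with one fixed daily threshold.
- Label moderate-to-vigorous minutes, the unscaled weekly total and the green activity measures as secondary. Under Hypothesis 2, say main outcome for this hypothesis instead of primary outcome.

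This is a change of wording before outcomes are analysed. It needs no new data and leaves 450 and 620 as they are. The cost is that the unscaled weekly total is no longer the headline. Scaling the total, rather than dropping it, stays closest to the reason the protocol gives for choosing it.

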### Mobility and park contact measured using GPS data

GPS units (Canmore) will be worn for one week, on an elastic belt with an accelerometer. At the end of the week of observation, data will be downloaded. To calculate the amount of time spent in ‘green PA’, these data will be linked with accelerometer data using time. Accelerometer data are then restricted using a threshold for PA and lux (> 400). Speed is calculated and data are further restricted by excluding speeds >25kmph. This results in total green PA. We will also use GPS data to calculate the actual contact time spent within view of the park [59] and usage of park. To calculate time spent within view of park, we will create ‘viewsheds’ around each park to determine all possible viewpoints from which the park can be seen, accounting for obstacles such as buildings, as we have done previously [60, 61]. To calculate usage of park, all GPS points located within 10 m of the park boundaries will be compiled to calculate time spent in park.

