
We will employ two weighting schemes to create individual-level visual exposures from the park measures. First, we will weight each exposure by the actual contact time spent within view of the park in the one-week observation time using the GPS data [59], as described previously. Second, we will calculate the percentage of the viewshed occupied by the park, as seen from the participant’s home by capturing a 360° image from the front door of the home location. We will then create weights using these measures, to be applied to each of the visual exposures above.

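### The GPS rule for time in the park counts every fix within 10 m of its boundary, so time at home beside the park, and to a small extent driving past, is recorded as park use

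*Protocol article*

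**What the plan says.** The section on mobility and park contact derives three measures from one week of GPS data.

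- **Green physical activity.** Accelerometer data are linked to GPS by time and limited by an activity threshold and by light above 400 lux. The last step is then stated: "Speed is calculated and data are further restricted by excluding speeds >25kmph. This results in total green PA".
- **Time in view of the park.** Here "we will create ‘viewsheds’ around each park to determine all possible viewpoints from which the park can be seen, accounting for obstacles such as buildings". No speed rule is given.
- **Time in the park.** Here "all GPS points located within 10 m of the park boundaries will be compiled to calculate time spent in park". No speed, light or own-home rule is given.

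The abstract gives the last two measures a central role: "Exposure to the INT will be assessed through visual contact time and time spent in the park using GPS data".

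**The concern.** The speed and light limits belong to a derivation that ends with green physical activity. Park time follows as a separate measure, and its rule takes all points. The 10 m margin covers ground outside the park, where houses, yards and roads may lie. A resident of that strip therefore gains park time by being at home, and a car on the edge road gains it by passing.

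At stake is one of the two measures that are meant to show how much contact residents have with the restored parks. The control description reports that only one of the nine parks was seen in use at the 2018 inventory, so true use starts close to zero. A few participants with many hours of false park time could then dominate a mean or a regression on this variable.

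**Working it through.** The plan gives no figure for this rule, so there is none to reproduce. It also gives no park sizes, home distances or traffic counts. What follows shows the size of the effect under stated assumptions.

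**Inputs from the protocol article.** The zone reaches 10 m from the boundary. The belt is worn in waking hours for seven days (stated for the accelerometer, which shares the belt with the GPS unit). Valid accelerometer data need at least 4 days of 8 to 10 h. Participants live within 500 m of a park. The target is 450 participants, 50 per park.

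**1. Home time credited as park time.** Hours = days × hours per day × share of wear time with home fixes in the strip. The share is assumed to be 10% to 50%.

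| Wear | 10% | 30% | 50% |
|---|---|---|---|
| 4 days × 8 h = 32 h | 3.2 h | 9.6 h | 16 h |
| 7 days × 10 h = 70 h | 7 h | 21 h | 35 h |

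**2. Effect on a park's mean.** With 50 participants per park, one such person adds between 3.2/50 = 0.064 h (about 4 min) and 35/50 = 0.7 h (42 min) per week to that park's average. If nearly everyone else is at or near zero, that one person can supply most of the recorded park time.

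**3. Vehicle passes.** Seconds per pass = (frontage + 20 m) / (speed in km/h ÷ 3.6), for an assumed frontage of 50 to 200 m and speed of 25 to 50 km/h.
- Shortest: 70 / 13.89 = 5.0 s. Longest: 220 / 6.94 = 31.7 s.
- At an assumed 14 passes a week: 14 × 5.0 / 60 = 1.2 min to 14 × 31.7 / 60 = 7.4 min.

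**4. Share of the counted area that lies outside the park.** For an assumed square park of side L, the outer strip is 40L + 100π m², and its share is (40L + 100π) / (L² + 40L + 100π).
- L = 50 m: 2,314 / 4,814 = 48%
- L = 100 m: 4,314 / 14,314 = 30%
- L = 200 m: 8,314 / 48,314 = 17%

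**5. How many participants might live in the strip.** The strip is compared with the recruitment area, using the same square parks.
- Against a 500 m zone around the park, of area 2,000L + 250,000π m²: 2,314 / 885,398 = 0.3% (L = 50 m) to 8,314 / 1,185,398 = 0.7% (L = 200 m). If homes were spread evenly, that is about 1 to 3 of 450.
- If the 16-cell grid is read as 4 × 4 cells with sides of 120 m, it is 480 m square: 2,314 / 230,400 = 1.0% to 8,314 / 230,400 = 3.6%, or about 5 to 16 of 450.

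Home time is the material error for those affected. Vehicle time is minor.

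**The case against.** The best defence is that little depends on this. Few homes can lie within 10 m of a park when recruitment reaches 500 m. The comparison is of change over time, so a stable home offset in the same person largely cancels. Park use is also observed directly, by SOPARC, in all nine parks. The listed analyses name no hypothesis test on time in the park, and total activity does not use it. Parcel rules and dwell times are details that an article may leave to the full protocol.

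Most of this stands as a limit on size. It does not remove the point, because the article does not merely leave a detail out: it states a rule that takes all points. Cancellation is also only partial. Hours at home differ between measured weeks, and under the fallback to repeated cross-sections the same people are not compared.

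Three stronger readings are tempting, and the documents support none of them.

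- **Time in view is contaminated in the same way.** Seeing the park from home is an intended exposure. The background treats passive sight of greenery as a possible route to lower stress, and one planned weighting is built from the home: "we will calculate the percentage of the viewshed occupied by the park, as seen from the participant’s home". View time serves as a weight: "we will weight each exposure by the actual contact time spent within view of the park in the one-week observation time using the GPS data". The park features being weighted can change with restoration even if home time does not. The viewsheds also model buildings as obstacles. A 400 lux filter would remove window and evening views that the study means to count.
- **Park use mostly measures where people live, so the two groups could look alike after a successful restoration.** Only homes inside the strip are affected, their number is not given, and independent observation of park use remains.
- **Points deep inside a park are not counted.** The sentence exists to measure time in the park. Its natural meaning is the park plus a 10 m margin.

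**Conclusion.** The point holds for time in the park only. As written, the rule credits at-home time in the 10 m strip as park use. On the assumed shares this is about 3 to 16 h/week per affected person at minimum accelerometer wear and 7 to 35 h/week at full wear, and vehicle passes add about 1 to 7 min/week. How many people are affected cannot be determined from the document, and it is probably a small number. Their weight comes from leverage: true use appears to be near zero at the outset, so a few large false values can dominate the GPS park-use measure. The primary comparison of total activity between intervention and control neighborhoods is untouched, and no change to the time-in-view measure is called for. The correction is worth making because one of the two named exposure measures is concerned and the remedy is cheap.

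**What to change.** Define time in the park as GPS points inside the park polygon plus the 10 m outward margin, stated as an allowance for GPS error. Exclude points on the participant's own parcel, and apply the 25 km/h exclusion that the section already uses for green physical activity. Add a sensitivity analysis that counts only points inside the boundary. Leave home viewing in the time-in-view measure, without a light filter.

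This changes processing rules only. GPS position and speed are already in hand, home location is known from recruitment, and parcel outlines would be matched to it. The rules are best fixed before the exposure data are analyzed. The cost is that a few true short or edge visits by residents who abut the park will be lost.
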